## Methods

The present study entitled the EPI-Family Health Study.

This study is an initiative to monitor different health parameters in the family environment. We will assess autonomic and cardiovascular systems (cardiac autonomic modulation, blood pressure and resting heart rate), bone mineral density, anthropometric indices, handgrip strength, mental health (quality of life, anxiety and depression symptoms and stress), self-reported morbidities and musculoskeletal pain outcomes. Lifestyle habits will include physical activity levels, sedentary behavior, sleep quality and time, eating patterns, smoking and alcohol consumption.

The invitation to participate in the study will be made through different means (social media, posters, folders, researchers going to schools). At the end of the evaluations, a didactic feedback will be prepared with the main results and a doubt channel will be made available where participants can be guided. This study will have a longitudinal design and the objective is for reassessments to take place annually. It is noteworthy that the present study is supported by the São Paulo Research Foundation (FAPESP; process: 2022/16437-8).

### Sample

The sample for this longitudinal study will consist of adults and children and adolescents aged 6–17 years. The study will be carried out in the city of Presidente Prudente, located in the southeast region of Brazil and which has approximately 230,000 inhabitants according to information from the Brazilian Institute of Geography and Statistics.

Sample recruitment will take place through flyers spread across the five regions of the city (north, south, east, west and central area) and also through social media (Facebook, Instagram, Whatsapp, radio, TV) and researchers going to schools to extend the invitation. The inclusion criteria will be considered: i) children, adolescents and parents who do not have a pacemaker (as it can influence the results of the assessment of cardiac autonomic modulation, ii) who carry out all the assessments proposed by the study; iii) who have not used any type of caffeinated or alcoholic beverage in a period of 12 h before the assessments.

To calculate the sample, a correlation of 0.31 was used based on the study by Christofaro et al. [15] for the relationship between the physical activity of parents and children, considering a power of 80% and an alpha error of 5%. Anticipating possible sample loss, an additional 10% will be added to this calculation, totaling a minimum number of 176 participants. However, as multiple regressions will be carried out in the present study, the sample size was increased by 20%, totaling a final sample number of 212 participants to be evaluated (106 children and/or adolescents and at least one of their parents to be evaluated). The intention of the present study is to carry out reassessments every twelve months.

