### Assessments

#### Health parameters

##### Cardiac autonomic modulation

The assessment of cardiac autonomic modulation will be carried out using heart rate variability (HRV). For this evaluation, the subjects will be instructed that 12 h before carrying out the experimental protocol they do not use alcoholic beverages and/or stimulants (coffee and tea), so that there is no direct influence on cardiac autonomic behavior [18].

For HRV analysis, heart rate will be recorded beat by beat for 30 min in a room with controlled environment (temperature − 21 to 24° C; relative air humidity − 50 to 60%) [18]. For this analysis, a strap to capture electrical impulses will be positioned on the distal third of the participant’s sternum and will capture the heart’s electrical impulses and transmit such information through an electromagnetic field to a Polar brand heart rate receiver, model V800 (Polar Electro Oy, Kempele, Finland), which will be positioned on a of the participant’s wrists.

Participants will be placed in a supine position at rest and with spontaneous breathing. The series of RR intervals obtained will initially be submitted to digital filtering using the Kubios HRV® software (Biosignal Analysis and Medical Image Group, Department of Physics, University of Kuopio, Finland) with a median filter and and interval correction with a cubic spline interpolation method. After preprocessing the absence of artifacts or cardiac arrhythmias that may interfere with the HRV analysis will be observed through the visual analysis of the temporal series. In the present study, only series in which sinus beats are equal to or higher than 95% will be considered [19].

For HRV analysis, which will be carried out using linear methods (analyzed in the time and frequency domains) and non-linear methods, 1000 beats from the most stable period of the tracing will be used. For analyzes of linear and non-linear methods, the Kubios HRV® software (Biosignal Analysis and Medical Image Group, Department of Physics, University of Kuopio, Finland) and Visual Recurrence Analyzes (VRA) version 4.9 (Eugene Kononov, USA) will be used.

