### Lifestyle habits

#### Intensity of physical activity

The different intensities of physical activity will be measured objectively through the Actigraph GT3X accelerometer (ActiGraph, LLC, Pensacola, FL, USA), which is a light, portable, small, easy-to-use instrument designed to be positioned on the subject to record movements in the three orthogonal planes: vertical, horizontal anteroposterior and mediolateral. The accelerometers will be positioned laterally at waist height for those evaluated, who will remain with the equipment for four full days (three weekdays and at least one weekend day) [30]. Participants will be instructed to use the equipment throughout the day, removing it only when there is contact with water (taking a shower or swimming, for example) and during sleeping hours.

The ActiLife 6 program (ActiGraph, LLC, Pensacola, FL, USA) will be used to clean the data. Each data sample, determined by counts, will be summarized considering a specific time interval, this specific interval is designated as epoch, and lasts 60 s. The 60-second period was selected because it is the closest to the low-intensity, long-duration activity pattern [31]. Consecutive hours of zero counts and days with less than 10 h of monitoring will be excluded [32].

We will use the cutoff point recommended by Troiano et al. [30] to analyze the different intensities of physical activity. Light physical activity will be defined as 101–2019 counts per minute, moderate physical activity will be defined as counts between 2020 and 5998, vigorous physical activity will be defined as counts greater than ≥ 5999 cpm counts per minute. Activities below 100 counts per minute will be considered time in sedentary behavior.

Children and adolescents will be classified according to the cutoff points recommended by Evenson et al. [33], light physical activity will be considered 101–2295 counts per minute, moderate physical activity will be defined as 2296–4011 counts per minute and vigorous physical activity ≥ 4012 counts per minute. Activities below 100 counts per minute will be considered sedentary behavior.

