### Potential challenges

Like all longitudinal studies, which follow participants for a long period, there is naturally sample loss due to a series of factors, such as withdrawal from participating in the study, moving to another city, among others. However, some strategies were designed to mitigate sample losses as: (1) Will be to provided a didactic report with all the assessments carried out, indicating to the participants all the results of the health parameters carried out; (2) We will try to maintain contact via social media so that rapprochement with participants always occurs.

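### Inclusion criterion (ii) requires completion of every assessment, so eligibility depends on compliance after enrolment and selects adherent families

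*Protocol article*

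**What the plan says.** The Sample section of the protocol article gives three inclusion criteria: (i) no pacemaker, (ii) people "who carry out all the assessments proposed by the study", and (iii) no caffeinated or alcoholic drinks in the 12 hours before the assessments.

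The Data collection section sets the order of events. The interview, blood pressure, resting heart rate and heart rate variability come at the first visit, where the accelerometer is handed out. Anthropometry and DEXA come at a later visit, when the device is returned. The section on intensity of physical activity asks for four full days of wear.

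The sample size in the Sample section rests on a parent-child correlation ("a correlation of 0.31 was used") with 80% power and 5% alpha. On loss it says: "Anticipating possible sample loss, an additional 10% will be added to this calculation, totaling a minimum number of 176 participants". A further 20% for multiple regression brings the total to 212 participants, or 106 children with at least one parent each. No completion rate is given, and nothing is said about replacing people who do not complete.

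On follow-up, the same section says: "The intention of the present study is to carry out reassessments every twelve months". The Potential challenges section adds: "Like all longitudinal studies, which follow participants for a long period, there is naturally sample loss due to a series of factors".

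**The concern.** An inclusion criterion should be decidable when a person enters the study. Criterion (ii) is decided by what the person does afterwards, so it acts as a completers-only rule placed among the eligibility criteria.

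Two harms follow. The first is selection. The study asks how lifestyle and health in parents relate to those of their children, and whether this differs between more and less active parents. Willingness to wear a device for four days and make a second visit is plausibly related to activity, health and socioeconomic status. Selecting on it can narrow the range of the variables under study and distort the contrast between active and inactive parents. A larger sample does not cure that.

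The second is waste. Someone with sound blood pressure, sleep and diet data who misses the return visit fails the criterion and leaves every analysis. The pair goes too, unless the other parent also took part.

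**Working it through.** **Timing.** With only the baseline battery counted, there are about three points at which a person can fail to comply: the first visit, the device wear and the return visit. The last two fall after enrolment. The criterion is therefore undecidable at enrolment even on its narrowest reading.

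**Reproducing the plan's sample size.** The inputs, all from the Sample section, are r = 0.31, 80% power, 5% alpha (taken as two-sided, since the sides are not stated), +10% and +20%.

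- Pairs: n = ((1.960 + 0.842) / atanh(0.31))² + 3 = 79.4, so 80 pairs.
- Participants: 80 × 2 = 160.
- With 10% for loss: 160 × 1.10 = 176, as stated.
- With 20% for regression: 176 × 1.20 = 211.2, so 212, or 106 pairs, as stated.

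A one-sided test gives 64 pairs and does not lead to 176. The stated figures are reproduced, and the arithmetic of the sample size is not in question.

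**Loss of pairs under the criterion.** Let d be the proportion of individuals who do not complete. The document gives no value, so d is an assumption and a range is shown. With one parent per child:

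- If parent and child fail independently, pairs kept = 106 × (1 − d)².
- If failure is fully shared within families, pairs kept = 106 × (1 − d).
- Power = Φ(atanh(0.31) × √(n − 3) − 1.96), for the simple correlation.

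| d per person | Pairs lost, independent | Pairs left | Power | Pairs lost, fully shared | Pairs left | Power |
|---|---|---|---|---|---|---|
| 0% | 0% | 106 | 90% | 0% | 106 | 90% |
| 5% | 9.8% | 96 | 87% | 5% | 101 | 89% |
| 10% | 19% | 86 | 83% | 10% | 95 | 87% |
| 20% | 36% | 68 | 73% | 20% | 85 | 83% |

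**Where the margins lie.** Under independence, about 5% non-completion per person uses up the 10% allowance: 88 pairs × 0.95² = 79.4. The full 106 pairs stay at or above the required 80 up to a pair loss of 1 − 80/106 = 24.5%. Under independence that is 1 − √(80/106) = 13% per person. The extra room comes from the 20% added for multiple regression, which was meant for another purpose.

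**The case against.** **The size of the loss.** Every completion rate above is assumed. Parent and child are likely to fail together, which moves the result towards the right-hand columns, where power stays above 80% even at 20% non-completion. Where two parents take part, losing one need not lose the pair. The study might also recruit until 212 people have completed; the text does not say. All of this stands. It limits the claim about numbers but does not touch the selection.

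**Later visits.** A reader might infer that anyone lost at an annual reassessment becomes ineligible in retrospect, so that the sample is conditioned on never dropping out. The literal wording allows this, but it is a strained reading. Reassessment is described as an intention, and the Potential challenges section treats withdrawals and moves as sample loss to be reduced, not as ineligibility. The point here rests on the baseline battery only.

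**Invalid recordings.** A reader might also infer that a failed recording removes the person from the study. The accelerometer rule ("Consecutive hours of zero counts and days with less than 10 h of monitoring will be excluded") drops hours and days, and the heart rate variability rule ("only series in which sinus beats are equal to or higher than 95% will be considered") drops series. Neither drops people, and carrying out an assessment is not the same as yielding valid data.

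**Multiplying many failures.** Treating each of the many instruments as a separate, independent chance of failure would give much larger losses. Most of them share one visit, so that model is not supported.

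**Abstinence.** Criterion (iii) could be read as screening out habitual users of caffeine or alcohol. The section on cardiac autonomic modulation makes it an instruction given before the test, and habitual intake is measured as weekly frequency. Restriction of these exposures does not follow from 12 hours of abstinence. What remains is a mismatch: the Sample section makes it a condition of eligibility before the assessments in general, while the only reason given concerns the autonomic recording.

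**Missing detail.** Analysis sets and the handling of missing data are commonly left to a fuller document. The objection here is to a rule that the article does state.

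**Conclusion.** The point holds as a design fault that should be fixed. Criterion (ii) makes eligibility depend on behaviour after enrolment, and following it as written selects adherent families and throws away usable data. This conclusion needs no assumed rate. That the selection biases the parent-child associations is plausible rather than demonstrated: the document gives nothing from which its size or direction could be derived.

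The effect on numbers is conditional. For 5% to 20% non-completion per person, independent within pairs, 9.8% to 36% of pairs are lost and power for r = 0.31 falls to between 87% and 73%. With fully shared non-completion the range is 89% to 83%. The 10% allowance can be exceeded, but a reader who concludes that it will be, or that the study is underpowered, goes beyond what the document supports. The power figures concern a simple correlation, not the adjusted regressions.

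**What to change.** Delete (ii) from the inclusion criteria and define eligibility only on facts known at enrolment. Analyse each outcome, with the regressions already named in the Statistical analysis section, in all parent-child pairs who have that outcome's measurements, and report n for each analysis. Compare people who completed the battery with those who did not on the characteristics recorded at the first visit.

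As a secondary change, reconcile criterion (iii) with the section on cardiac autonomic modulation by stating the 12-hour abstinence as a condition of that recording rather than of entry to the study.

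The cost is a small change of wording and no additional measurements. The downside is that n will differ slightly between analyses. The change should be made before data from non-completers are set aside, because selection cannot be examined later if those data are not kept.

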### Ethical considerations

The present study was approved by the Ethics and Research Committee of the São Paulo State University (UNESP) (CAAE: 59261422.2.0000.5402). All participants will have to sign the consent form agreeing to participate in the study. Children and adolescents will also sign a consent form agreeing to participate in the study. The present study is registered on the clinicaltrials.gov platform (protocol: NCT06248164).

### Data collection

After sample recruitment has been carried out, data collection will begin. Graduate and undergraduate students will carry out data collection. Before data collection, all students will receive training for assessments in all procedures used in this study (questionnaires, accelerometers, heart rate monitors and DEXA).

Initially, participants will come to the São Paulo State University (UNESP). In this first evaluation, the interview will be carried out through the application of a questionnaire, in which the evaluators will collect data face to face with the participant. They will also carry out an assessment of blood pressure, resting heart rate and cardiac autonomic modulation through heart rate variability and at the end of this assessment the accelerometer will be given to the research participant with explanations and how this instrument should be used. Accelerometer collection procedures are described below:

(i) The individual will receive the accelerometer and one of the evaluators will explain how the device works (how to use and when to remove it) and will also leave a small manual with information about the device; (ii) Based on the cell phone number entered in the registration form of each subject who has the accelerometer, messages will be sent via SMS and/or WhatsApp reminding the study participant to use the accelerometer. If the subject only has a home telephone, the evaluator responsible for that subject will make a call reminding the subject to put on the device; (iii) On a pre-scheduled date, the participant will come to UNESP, deliver the accelerometer and carry out the final assessment, consisting of anthropometry (weight, height, waist circumference) and measurement of body composition using DEXA.

### Assessments

#### Health parameters

##### Cardiac autonomic modulation

The assessment of cardiac autonomic modulation will be carried out using heart rate variability (HRV). For this evaluation, the subjects will be instructed that 12 h before carrying out the experimental protocol they do not use alcoholic beverages and/or stimulants (coffee and tea), so that there is no direct influence on cardiac autonomic behavior [18].

For HRV analysis, heart rate will be recorded beat by beat for 30 min in a room with controlled environment (temperature − 21 to 24° C; relative air humidity − 50 to 60%) [18]. For this analysis, a strap to capture electrical impulses will be positioned on the distal third of the participant’s sternum and will capture the heart’s electrical impulses and transmit such information through an electromagnetic field to a Polar brand heart rate receiver, model V800 (Polar Electro Oy, Kempele, Finland), which will be positioned on a of the participant’s wrists.

Participants will be placed in a supine position at rest and with spontaneous breathing. The series of RR intervals obtained will initially be submitted to digital filtering using the Kubios HRV® software (Biosignal Analysis and Medical Image Group, Department of Physics, University of Kuopio, Finland) with a median filter and and interval correction with a cubic spline interpolation method. After preprocessing the absence of artifacts or cardiac arrhythmias that may interfere with the HRV analysis will be observed through the visual analysis of the temporal series. In the present study, only series in which sinus beats are equal to or higher than 95% will be considered [19].

For HRV analysis, which will be carried out using linear methods (analyzed in the time and frequency domains) and non-linear methods, 1000 beats from the most stable period of the tracing will be used. For analyzes of linear and non-linear methods, the Kubios HRV® software (Biosignal Analysis and Medical Image Group, Department of Physics, University of Kuopio, Finland) and Visual Recurrence Analyzes (VRA) version 4.9 (Eugene Kononov, USA) will be used.

### Blood pressure and resting heart rate

Blood pressure will be assessed using an Omron automatic blood pressure measuring device (Model HEM-742, Japan). Before the first blood pressure measurement is assessed, individuals will remain seated at rest for five minutes, with their legs uncrossed, and will not be able to talk during this time. Two blood pressure measurements will be taken, and the average will determine the systolic and diastolic blood pressure value of the subject evaluated. These procedures are in line with the American Society of Cardiology [20].

### Body composition

General and abdominal obesity will be determined by weight and height measurements (which will determine the calculation of BMI in general obesity) and by waist circumference, respectively. The percentage of fat, fat-free mass and density and bone mineral content will be estimated using dual-energy x-ray absorptiometry (DEXA, Lunar Prodigy; General Electric Healthcare, Little Chalfont, Buckinghamshire, United Kingdom). The equipment’s own software will be used (GE Medical System Lunar, version 4.7).

### Handgrip strength

Handgrip strength will be assessed using a manual dynamometer in which two handgrip measurements will be taken on each arm. The highest value observed will be considered as an indicator of the strength level.

### Quality of life (QoL)

To assess QoL, the Medical Outcomes Study SF-36-Item Short Form Health Survey (SF-36) instrument will be used in the parents. The SF-36 is made up of 36 items that cover eight domains regarding QoL: functional capacity, physical limitations, body pain, general perception of health, vitality, social aspects, emotional limitations, mental health. The scores for this questionnaire range from 0 to 100 and the higher the score, the better the QoL for the analyzed domain [21].

The quality of life of children and adolescents will be assessed using the KIDSCREEN-52 questionnaire [22]. This instrument has 52 questions that analyze ten different domains (health and physical activity; feelings; emotional state; self-perception; autonomy; family environment; financial aspect; friends and social support; school environment and provocation / bullying) in pediatric populations. Based on the KIDSCREEN-52 scores, these values will be recoded to a scale of 0 to 100, where the higher the value, the better the undeveloped QoL domains. This instrument is validated for use with young Brazilians [23].

### Anxiety and depression

Symptoms of anxiety and depression will be analyzed using the Hospital Anxiety and Depression Scale (HADS). This instrument consists of 14 questions in total, half of which assess symptoms of anxiety and the other half of depression [24]. The score for each item varies from 0 to 3, providing a total score of 21 for each of the outcomes analyzed, and the higher the value, the worse the condition of the evaluated participant. This scale is also validated for use with young people [25].

